### Sample size

The sample size was calculated using the primary outcome based on a minimum clinically important difference (MCID) at primary endpoint allowing for power at 0.80 and a two sided alpha at 0.05. The primary outcome is incidence of major depression across the 12 months follow-up. Assuming that the MCID is an absolute risk reduction in incidence of major depressive episodes of 10% based on previously published consensus [55] and that incidence of major depressive episodes will be 25% in the usual practice arm, paralleling previous studies in this high-risk sample [18, 19], and assuming 20% follow-up attrition, then conservatively we require n=324 per arm, giving a total sample required of 648.

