### Randomisation, intervention delivery and masking

Participants will be randomised (in a 1:1 ratio) to the two intervention arms. Randomisation will be conducted automatically by means of a custom-built secure web service created and managed by the Exeter Clinical Trials Unit (ExeCTU), which interfaces with the trial database, and which will be independent of the trial researchers. To promote balance across key participant characteristics across intervention arms, randomisation will be stratified according to recruitment site (each of the six funded partner universities plus an “other” university category for students recruited elsewhere), and history of depression (no history vs past history of depression – given that this is a strong predictor of future depression and was used previously) [19]. Stratification will be used (on these two variables) and blocking will be used with minimum block size of 4 and maximum block size of 6, occurring at random to maintain concealment.

All the online recruitment and randomisation will be automated and independent of trial researchers. The Exeter CTU EDC system will contact an unblinded team member (administrator/therapist) indicating when an individual [by study ID] has been randomized to the active intervention. This team member will then access the relevant details in the EXCTU database and manually set up the participant in the mobile app intervention using administrator rights via the treatment platform dashboard. An email will also go to the participant indicating the condition to which they are randomised and informing them what to expect. The relevant unblinded team member will also monitor if the participant has accessed the intervention and check if any difficulties and encourage to sign-up.

All assessments will be routinely collected online using the EDC following automated reminders, without the involvement of researchers. Site researchers will be blind to treatment allocation. Site researchers will prompt all participants to complete follow ups by phone and text if they do not respond to the automated email reminders. Any unblinding in contact with a site researcher would be logged as a protocol deviation and only a researcher that remained blind will be able to prompt future follow-up from that participant.

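### The stated 324 per arm does not follow from the stated inputs, which give 313 or 338; it equals 270 × 1.2, though power stays near 80%

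*Protocol article*

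**What the plan says.** The Sample size section of the protocol article gives every input to a two-proportion calculation. The outcome is binary: "The primary outcome is incidence of major depression across the 12 months follow-up". The design allows for error rates as follows: "allowing for power at 0.80 and a two sided alpha at 0.05". The control assumption is that "incidence of major depressive episodes will be 25% in the usual practice arm", and the target is an "absolute risk reduction in incidence of major depressive episodes of 10" percentage points, so 15% in the app arm. The section on randomisation, intervention delivery and masking adds equal allocation: "Participants will be randomised (in a 1:1 ratio) to the two intervention arms".

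The result is then given in one step: "assuming 20% follow-up attrition, then conservatively we require n=324 per arm, giving a total sample required of 648". The section does not report the number before attrition, the formula, whether a continuity correction was used, or how the attrition allowance was applied. The section headed Statistical analysis plan bases the primary analysis on complete outcome data, so participants lost to follow-up drop out of the primary comparison.

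**The concern.** A reader who has all the inputs should be able to reproduce the output. Neither standard version of the two-proportion calculation gives 324 once 20% loss is properly allowed for.

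To finish with a required number *n* when a fraction *d* is lost, one must recruit *n*/(1 − *d*). Multiplying by (1 + *d*) recruits too few, because the loss applies to everyone recruited and not only to the number required. The stated figure has the look of that slip.

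The power claim for the primary outcome is at stake, together with the assurance that the target is conservative. Whether that assurance is true depends on which calculation lies behind the number, and the text does not say.

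**Working it through.** **Inputs.** p₁ = 0.25, p₂ = 0.15, difference 0.10, mean p̄ = 0.20, two-sided α = 0.05 (z = 1.960), power 0.80 (z = 0.842) and attrition 20% come from the Sample size section. The 1:1 ratio comes from the randomisation section.

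**Evaluable number per arm, no continuity correction.**

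n = [1.960·√(2·0.20·0.80) + 0.842·√(0.25·0.75 + 0.15·0.85)]² / 0.10²
= [1.960·0.5657 + 0.842·0.5612]² / 0.01 = 249.98, so **250**.

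**Evaluable number per arm, with continuity correction.**

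n_c = (n/4)·[1 + √(1 + 4/(n·0.10))]² = (249.98/4)·(1 + 1.0770)² = 269.6, so **270**.

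**Reproducing the stated figure.** 270 × 1.2 = **324**, and 2 × 324 = 648. The match is exact.

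**Dividing attrition out instead.**

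| Basis | Evaluable n | n / 0.8 (per arm; total) | n × 1.2 |
|---|---|---|---|
| No continuity correction | 250 | 313; 626 | 300 |
| Continuity correction | 270 | 338; 676 | **324** |

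Other formulas with the same inputs, divided by 0.8, give per arm:

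- unpooled variance or arcsine: 248, so 310
- average variance: 252, so 315
- log odds ratio: 256, so 320
- log risk ratio: 261, so 327
- unpooled variance with continuity correction: 267, so 334
- Fisher's exact test: about 268, so about 335

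None gives 324. The average-variance, log-odds-ratio and log-risk-ratio results lie within 3% of it.

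**What 324 delivers.** 324 × 0.8 = 259.2, so 259 evaluable per arm.

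- *Uncorrected.* z = (0.10 − 1.960·√(0.32/259)) / √(0.315/259) = (0.10 − 0.0689)/0.0349 = 0.892, power **81.4%**.
- *Continuity-corrected.* Subtract 1/259 = 0.0039 from the numerator: z = 0.781, power **78.3%**. Fisher's exact test gives 78.6%.
- *Log odds ratio.* The log odds ratio is 0.636 and the variance term is 1/(0.25·0.75) + 1/(0.15·0.85) = 13.18. z = 0.636/√(13.18/259) − 1.960 = 0.860, power **80.5%**.

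With 259 per arm, the reduction from 25% that is detectable with 80% power is 9.8 points uncorrected and 10.2 points corrected. For 324 to leave 270 evaluable, attrition could be at most 1 − 270/324 = 16.7%, below the planned 20%.

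**The case against.** The strongest reply is that the multiplication by 1.2 is inferred. The article prints neither 270 nor a continuity correction, and one exact match found by trying combinations of formulas is not a stated derivation. A journal article also condenses its full protocol, where the formula may appear. This stands, and it limits what can be said about how 324 arose. It does not remove the mismatch: the article prints a full set of inputs and a result, and neither standard calculation connects them.

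A second reply is that on the uncorrected basis 313 per arm is enough, so 324 has 11 to spare and could fairly be called conservative. This also stands. A blanket instruction to delete that word would be wrong.

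A third reply is that the only shortfall arises under continuity-corrected or exact tests. The planned primary analysis uses multilevel mixed-effect models, and no continuity correction is mentioned. The log-odds-ratio approximation, which is closer to such a model, needs 256 evaluable per arm, and 259 meets that. This stands too, and it shows that the 78% describes a planning formula and not the power of the planned analysis.

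A reader might infer from the 78% that the trial is underpowered, or that 28 more participants (676 − 648) are needed. The documents do not support either. On the uncorrected and log-odds-ratio calculations the planned number reaches 80% with the full 20% loss.

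**Conclusion.** The stated number does not follow from the stated inputs. With attrition divided out, the answer is 313 per arm without continuity correction or 338 with it. The most likely origin of 324 is 270 inflated by 1.2, but this is an inference from an exact match.

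The practical effect is small. On the basis that appears to generate 324, power is 1.7 points below the claimed 80% (78.3%). On the uncorrected basis it is 1.4 points above (81.4%). These figures take the 25% and 15% incidences and the 20% attrition as given, and treat the comparison as a simple one of two independent proportions. They are not a calculation for the multilevel model itself.

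This is an error in how the sample size is derived or reported. It gives no reason to change the recruitment target.

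**What to change.** Keep 648. Replace the closing sentence of the Sample size section with one that states that 324 per arm with 20% attrition leaves 259 evaluable per arm, names the formula used, and gives its power for 25% against 15% at two-sided 5%: 81% without continuity correction, or 78% with it. Give the pre-attrition number as well (250 or 270), and make clear that this is a planning approximation, so that the sentence is not read as replacing the planned mixed-effect model.

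The word 'conservatively' should depend on that choice. Keep it if the uncorrected basis, with 313 required, is stated. Remove it if the continuity-corrected basis, with 338 required, is used.

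The cost is a few lines of text, with no extra participants and no change to the conduct of the trial.

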### Statistical analysis plan

The primary analyses will be intention-to-treat (ITT) analyses [56] (i.e. all participants will be included in the analyses according to their randomised allocation) and based on complete case outcome data. The primary inferential analyses will compare across trial arms for the primary and continuous secondary outcomes at 12-months follow up using multilevel mixed-effect models, which enable us to examine nested hierarchies in the data (individual, intervention, university), across time (examining pre-to-post change), to capture dependencies in the data, to investigate individual trajectories (random intercepts, random slopes), and which have less restrictive assumptions re missing data.

Secondary analysis will be undertaken using both Complier Average Causal Effect models and multiple imputation:Complier Average Causal Effect (CACE) analysis [57, 58] to provide an estimate of a treatment effect accounting for pre-specified per protocol adherence and compliance with the treatment, whilst retaining the benefits of randomisation.Multiple imputation following the examination of the pattern of missing outcomes to impute primary and secondary continuous outcomes. Imputation models will be informed by treatment arm, baseline scores, other covariates to be included in the model, and other baseline characteristics found to predict outcome or propensity for missingness (logistic regression models will be used to investigate the associations between baseline characteristics and missingness).

Secondary analyses will be undertaken including:Models will be estimated for the primary and secondary outcomes at 3- and 12-month follow-up and will include the covariates adjusted for in the linear regression models.Cox regression models will be undertaken to investigate between group differences in the time until a major depressive episode.Mediation analyses will be undertaken to gain insight into mechanisms that could explain the potential effect of the interventions on primary outcomes. We will use modern causal inference methods using structural equation modelling or parametric regression models to assess mediation effects [59]. In addition, we will investigate potential moderation of the interventions by site and history of depression.The results of all models will be compared to primary analysis complete case ITT results.Analyses will be undertaken by a statistician blinded to group allocation and using Stata v.17.

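### The primary analysis is called intention-to-treat with everyone included yet rests on complete cases; with 20% attrition assumed, both cannot hold, and the missing-data rule needs one clear statement

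*Protocol article*

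**What the plan says.** All of the relevant text is in two sections of the protocol article.

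- **Statistical analysis plan, analysis set.** The primary analyses are intention-to-treat, explained as "all participants will be included in the analyses according to their randomised allocation) and based on complete case outcome data". The section ends by using the same label again: "The results of all models will be compared to primary analysis complete case ITT results".
- **Statistical analysis plan, model.** The arms are compared "for the primary and continuous secondary outcomes at 12-months follow up using multilevel mixed-effect models". One reason given for these models is that they are ones "which have less restrictive assumptions re missing data".
- **Statistical analysis plan, missing data.** "Secondary analysis will be undertaken using both Complier Average Causal Effect models and multiple imputation". The imputation inputs named are treatment arm, baseline scores, other model covariates, and baseline characteristics that predict outcome or missingness. The 3-month outcomes are not named.
- **Sample size.** The calculation is made "allowing for power at 0.80 and a two sided alpha at 0.05" and "assuming 20% follow-up attrition", with the result that "we require n=324 per arm, giving a total sample required of 648".

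Follow-up is at 3 and 12 months. The LIDAS, PHQ-9, worry and rumination measures are collected at both (Table 2).

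**The concern.** An analysis of everyone randomised and an analysis of complete cases coincide only if nobody is lost, and the plan expects one in five to be lost. The justification for the model has the same problem. A likelihood-based mixed model relaxes the missing-data assumption because people with some follow-up still contribute. If entry requires the 12-month outcome, someone seen at 3 months and then lost contributes nothing, and the assumption becomes the stronger one that the restriction implies. For the primary outcome, the discarded 3-month LIDAS bears directly on incidence over the 12 months.

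What is at stake is the headline estimate and its label. Participants know their allocation, the outcome is self-reported, and an unblinded team member checks access and encourages sign-up in the app arm only. Dropout that relates to symptoms differently in the two arms is therefore plausible. A complete-case contrast would carry the resulting bias while being reported as intention-to-treat in all participants.

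**Working it through.** **1. The plan's own sample size.** Inputs from the sample size section: 25% against 15% (an absolute reduction of 10 points), two-sided alpha 0.05, power 0.80, 20% attrition.

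- Without continuity correction: n = [1.96·√(2·0.20·0.80) + 0.842·√(0.25·0.75 + 0.15·0.85)]² / 0.10² = 250 per arm.
- With continuity correction: (250/4)·[1 + √(1 + 4/(250·0.10))]² = 270 per arm.
- 270 × 1.2 = 324, which reproduces the stated figure. Dividing by 0.8 gives 313 (from 250) or 338 (from 270).

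**2. Who leaves under a 12-month complete-case rule.** 0.20 × 648 = 129.6, so about 130 leave and about 518 remain (259 per arm). If attrition were different (assumption): 10% is 65, 30% is 194, 40% is 259.

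**3. Power is not the main issue.** At 259 per arm, power for 25% against 15% is about 81% (78% with continuity correction). The sample size already allows for the loss.

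**4. What the missing could do, without a model.** Assume observed risks of 25% and 15%, with 20% missing in each arm. The difference in all randomised is 0.8 × 10 + 0.2 × (risk in missing controls − risk in missing app users), in points.

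| Risk in missing controls | Risk in missing app users | Difference in all randomised |
|---|---|---|
| 25% | 15% | 8 + 2 = 10 points |
| 25% | 25% | 8 + 0 = 8 points |
| 25% | 50% | 8 − 5 = 3 points |
| 0% | 100% | 8 − 20 = −12 points |
| 100% | 0% | 8 + 20 = +28 points |

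The last two rows are logical bounds and not expectations.

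**5. A simulation with no true effect.** Every input in this step is an assumption, apart from the control risk and a loss close to the planned one. Baseline and 3-month severity are standard normal with correlation 0.5. The event log-odds are 0.2 × baseline + 0.9 × 3-month severity, set to a risk of about 25%. Loss is about 18–20%, with log-odds depending on 3-month severity. Negative values favour the app. Small spreads reflect the exact loss rate and intercepts.

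| Dropout slope per SD, app / control | Complete-case bias (points) |
|---|---|
| 0.7 / 0.2 | −1.5 to −1.7 |
| 0.4 / 0.2 | −0.5 to −0.6 |
| 0.45 / 0.45 | about 0 |
| 0.2 / 0.7 | +1.6 to +1.7 |

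**6. Would the imputation as described repair this?** In the 0.7 / 0.2 scenario, imputing within arm from baseline alone leaves −1.2 of −1.7 points: 1.2/1.7 = 0.71, so about 70% of the bias remains. Adding 3-month severity removes it. That is by construction, since dropout here depends only on 3-month severity, which the simulation treats as known for everyone. People lost before 3 months would not be helped in this way.

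**The case against.** The strongest reply is that complete case is undefined and can be read generously. The next sentence describes models across time with random intercepts and slopes, which fits using every observed outcome without imputation. Participants with only 3-month data would then stay, fewer than 130 would drop, and part of the missing-data advantage would survive. This stands. A reader might infer that the plan certainly discards everyone seen at 3 but not 12 months; the article does not say so.

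Second, missing data are not ignored. Multiple imputation, a check of what predicts missingness, and a comparison of every model with the primary result are all prespecified. This also stands, and it lowers the severity. Which analysis should be primary is partly a matter of judgement, since imputation rests on an untestable assumption too. But the headline estimate remains the complete-case one, and the inputs named for the imputation are baseline ones.

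Third, a reader might infer that the result will be biased in favour of the app. Nothing in the document fixes the size or direction: reversing the assumed slopes reverses the sign, and equal slopes give almost no bias.

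Fourth, analysis sets are often left to a fuller plan. That would answer a missing definition. Here the article states a rule, twice, that conflicts with its own description of who is included.

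**Conclusion.** The point holds as an internal contradiction in the primary analysis rule, and it should be fixed. Inclusion of all participants, restriction to complete cases, and reliance on the mixed model's weaker assumptions cannot all be true at 20% attrition. On the narrow reading about 130 of 648 are excluded; that is planned attrition and not an observed count. On the generous reading fewer are excluded and the complete-case label is wrong.

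The possible bias is moderate beside the 10-point difference the trial is designed to detect: within about ±1.7 points in the scenarios examined, and near zero when dropout depends on symptoms equally in both arms. Those figures rest on assumed slopes and illustrate a mechanism; they do not predict this trial's error. The issue is bias and labelling, not power.

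**What to change.** 1. Delete the clause that ties the intention-to-treat analysis to complete cases, and change the matching label at the end of the section.
2. Continuous outcomes: fit the mixed model by maximum likelihood to all available 3- and 12-month data from every randomised participant.
3. Binary primary outcome: base the intention-to-treat estimate on all randomised participants, using multiple imputation within arm that includes the 3-month LIDAS, PHQ-9, worry and rumination scores as well as the baseline variables. Promoting the imputation as now described is not enough, because a baseline-informed model would leave most of the bias illustrated above.
4. Keep complete case as a sensitivity analysis, define it, and do not describe it as including all participants.

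The cost is revised wording and a somewhat larger imputation model, which still assumes missing at random. No additional data collection is needed. Recruitment was still under way at publication, so the change can be made before unblinding.

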			**Follow-up (months)**	
**Web Assessment**		**Baseline**	**3**	**12**
Pre-screening	date of birth, self-reported mental health	✓		
Informed Consent		✓		
Socio-demographics	Age, sex, employment status, ethnicity, historic mental health problems	✓		
LIDAS	Incidence of current and past major depressive episode (primary outcome)	✓	✓	✓
Rumination	RRS-Brooding questionnaire; secondary outcome	✓	✓	✓
Worry	PSWQ questionnaire; secondary outcome	✓	✓	✓
Wellbeing	WEMWBS questionnaire; secondary outcome	✓	✓	✓
Depression	PHQ-9 questionnaire; secondary outcome	✓	✓	✓
Anxiety	GAD-7 questionnaire; secondary outcome	✓	✓	✓
Resilience	BRS questionnaire; secondary outcome	✓	✓	✓
Perceived Stress	PSS-4 questionnaire; secondary outcome	✓	✓	✓
Stressful Events	ASQ questionnaire; secondary outcome	✓	✓	✓
Use of mental health services and resources			✓	✓
Academic Outcomes		✓	✓	✓

Once consented participants have completed the baseline assessment, they will be randomised automatically by an independent computer system. Randomised participants will be informed of their randomisation allocation and signed up to use the relevant variant of the app via clinically trained members of the research team. The participant’s University email address is used for app set-up.

All participants will be followed up electronically at 3 months and 12 months post-randomisation. At each follow-up point, participants will be automatically sent emails and texts with links to enter their data into the EDC. Each assessment point will involve an automated weekly follow- up by email and then text and telephone follow-ups to participants who haven’t yet completed the EDC assessment at 3 months and 12 months. Tables 1 and 2 give an overview of all measurements. Figure 1 gives an overview of trial flow. Project researchers will be blind to treatment allocation but will be available to participants to answer queries about the trial or the assessments. Participants will receive honorariums for the completion of each of the brief mediator assessments occurring each week for 8 weeks post-randomisation, 3-month and 12-month follow-up assessments.

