Participants will be asked to complete brief measures each week for eight weeks after randomisation to provide potential mediators of change: a two-item measure of depression (PHQ-2) [50]; a two-item measure of anxiety (GAD-2) [51]; a single item measure of stress over the last week (scored 0 none to 4 very severe); six items from the Cognitive and Behavioural Response to Stress Scale [52] assessing the frequency and usefulness of use of cognitive reinterpretation, behavioural activation, and relaxation or meditation strategies; 3-item adaptations of the automaticity component of the Self-Report Habit Index [53] focused on assessing the extent to which worry and problem-solving respectively are each a habit (e.g., “something that I do automatically" “I do without thinking”) over the past seven days; 2-items from the Self-Compassion Scale-short-form [54]; 2 items from the RRS-Brooding 5-item questionnaire [40]; a one-item measure assessing self-efficacy (“In the last seven days I feel better prepared to handle situations I could not handle before” rated using a seven‐point Likert scale ranging from −3 (“absolutely not true), 0 (“neither nor”) to +3 (“absolutely true”) and a one-item measuring problem clarification (“In the last seven days, I understand myself and my problems better” rated using a seven‐point Likert scale ranging from −3 (“absolutely not true), 0 (“neither nor”) to +3 (“absolutely true”).

The following descriptive variables will be assessed only at baseline: age, gender, sexuality, year of study, course of study, family’s occupational status, country of birth.

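### The stated imputation model names no post-randomisation predictor, so it gives limited protection if dropout follows early symptoms

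*Protocol article*

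**What the plan says.** All the analysis text is in the protocol article, under Statistical analysis plan. The primary analysis is intention-to-treat and "based on complete case outcome data". It uses multilevel mixed-effect models that work "across time (examining pre-to-post change), to capture dependencies in the data".

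Multiple imputation is a secondary analysis, used "to impute primary and secondary continuous outcomes". On its predictors the article says: "Imputation models will be informed by treatment arm, baseline scores, other covariates to be included in the model, and other baseline characteristics", the last group being those found to predict outcome or missingness. On the search for such predictors it says: "logistic regression models will be used to investigate the associations between baseline characteristics and missingness". On how the secondary results will be used: "The results of all models will be compared to primary analysis complete case ITT results".

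Elsewhere the article schedules richer information. Under Baseline and follow-up assessments: "All participants will be followed up electronically at 3 months and 12 months post-randomisation". Table 2 ticks LIDAS, RRS-Brooding, PSWQ, PHQ-9 and GAD-7 at both follow-ups. Under Secondary outcomes: "Participants will be asked to complete brief measures each week for eight weeks after randomisation"; these include PHQ-2 and GAD-2 and are described as potential mediators.

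**The concern.** Apart from arm, every predictor that the article identifies is a baseline one. The model covariates are not listed, but the words that follow them (other baseline characteristics) suggest that they too are baseline. The variables likely to say most about 12-month depression, and about who leaves between months 3 and 12, are collected but appear neither in the imputation list nor in the missingness regressions.

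This matters because imputation is the plan's check on a complete-case primary result. Imputing from arm and baseline assumes that, given those variables, dropout is unrelated to how the participant fared after randomisation. If that is false, the imputed and complete-case results can be biased in the same direction by similar amounts, and their agreement would be read as reassurance.

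The 3-month LIDAS has a further claim. The primary outcome is incidence across the whole 12 months. A participant who reports a post-randomisation episode at 3 months and then misses the 12-month assessment has already had an incident episode. A model that does not see this can impute no episode for that person.

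**Working it through.** **The plan's own figure.** The article states no figure for the imputation. Its one related figure is the sample size (Sample size section): 25% v 15%, two-sided alpha 0.05, power 0.80, 20% attrition, 324 per arm.

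- Uncorrected: n = [1.960·√(2·0.20·0.80) + 0.842·√(0.25·0.75 + 0.15·0.85)]² / 0.10² = 250 per arm.
- With continuity correction: (250/4)·[1 + √(1 + 4/(250·0.10))]² = 270.
- 270 × 1.2 = 324, the stated figure. (Dividing by 0.8 gives 338.)
- With 20% loss, 324 × 0.8 = 259 per arm, power about 81% without the correction. The sample size is not at issue here.

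**Simulation 1: risk difference, 400,000 per arm.** From the article: incidence 25% v 15% and 20% average attrition. Assumed, because the article does not give them:

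- correlation r between baseline and 3-month symptoms of 0.3, 0.5 or 0.7;
- log odds of depression of 1.0 per SD of 3-month symptoms and 0.3 per SD of baseline;
- log odds of dropout of 0.7 or 1.0 per SD of symptoms, in both arms or in the app arm only;
- 3-month symptoms observed for everyone.

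Bias is the estimate minus the true difference of about 10 points; a positive value overstates the benefit. Each cell gives complete-case bias → bias after imputation from arm and baseline (share removed).

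| Attrition control/app; what drives dropout | r = 0.3 | r = 0.5 | r = 0.7 |
|---|---|---|---|
| 20/20; 3-month, 0.7, both arms | −0.67 → −0.56 (15%) | −0.65 → −0.42 (35%) | −0.68 → −0.28 (59%) |
| 10/30; 3-month, 0.7, both arms | 1.17 → 1.01 (13%) | 1.37 → 1.01 (26%) | 1.26 → 0.60 (53%) |
| 15/25; 3-month, 0.7, both arms | 0.28 → 0.27 (4%) | 0.29 → 0.23 (19%) | 0.29 → 0.16 (46%) |
| 20/20; 3-month, 0.7, app only | 1.73 → 1.49 (14%) | 1.80 → 1.26 (30%) | 1.85 → 0.87 (53%) |
| 15/25; 3-month, 0.7, app only | 2.01 → 1.73 (14%) | 2.20 → 1.55 (30%) | 2.21 → 1.06 (52%) |
| 15/25; 3-month, 1.0, app only | 2.87 → 2.51 (13%) | 2.89 → 2.06 (29%) | 3.19 → 1.65 (48%) |
| 10/30; baseline, 0.7, both arms | 0.61 → −0.04 | 0.92 → 0.05 | 1.04 → −0.02 |

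In the first six rows, adding the 3-month score left a bias of at most 0.12 points either way (91% to 110% removed, the spread being simulation noise). In the last row, baseline imputation is already unbiased to within 0.05 points.

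**Simulation 2: 324 per arm, analysis model adjusted for baseline.** Assumed: r = 0.5; dropout log odds of 0.9 per SD of 3-month symptoms in the app arm only; average attrition 13% (control) and 25.5% (app). There were 600 trials with 10 imputations each. Mean log odds ratios, Monte Carlo standard error about 0.01:

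- full data −0.699
- complete case −0.878, bias −0.179
- imputed from arm and the same baseline covariate −0.874, bias −0.175, so 1 − 0.175/0.179 = 2% removed
- imputed with 3-month symptoms added −0.702, bias −0.003, so 1 − 0.003/0.179 = 98% removed

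**3-month LIDAS.** If onsets were spread evenly over the year (an assumption), 25%/4 = 6.25% of controls would have an episode by month 3. With 20% attrition unrelated to outcome, 324 × 0.20 × 0.0625 ≈ 4 controls would have an episode by month 3 and no 12-month assessment. The number is larger if depressed participants leave more often, and smaller if some of them also miss month 3.

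**The case against.** Several stronger readings are tempting, and the article does not support them.

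- *The model uses only baseline data.* A reader might infer this, but the text says that the models are informed by the listed items and does not call the list exhaustive. No time point is given for the outcomes to be imputed. Imputing 3- and 12-month outcomes jointly would bring the 3-month measures in, and the text does not exclude it.
- *The imputation barely corrects the bias.* This depends on the dropout mechanism, on which the article is silent. At r = 0.7 about half the bias goes; if dropout follows baseline, essentially all of it does.
- *The binary primary outcome will be imputed as continuous.* The same section earlier speaks of primary and continuous secondary outcomes, so the adjective belongs to the secondary ones. Nothing is wrong there.

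It can also be said that auxiliary variables are a matter for the SAP, which is not shown. That would answer silence, but here the article states the type of predictor and confines the missingness regressions to baseline, and an SAP that follows it inherits the weakness.

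A further reply is that the mixed model across time already uses post-baseline data. The complete-case wording leaves this unclear. If it does, imputing from baseline alone makes a stronger missing-data assumption than the analysis it is meant to test.

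Two practical cautions stand. Students lost at 12 months may also have missed month 3, so the near-complete recovery above is a best case. A long auxiliary list would also overfit: five 3-month measures plus 2 × 8 = 16 weekly scores make 21 variables, against about 324 × 0.8 × 0.15 ≈ 39 observed app-arm events.

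**Conclusion.** The point holds in a conditional form. The article's imputation description names no post-randomisation predictor, although strong candidates are scheduled. If dropout follows early symptoms, the stated model removes about 4% to 59% of a complete-case bias of 0.3 to 3.2 points, and about 2% where the analysis model already adjusts for the same baseline covariate. Adding 3-month symptoms removes nearly all of the bias when they are observed. If dropout depends on baseline alone, the stated model is adequate.

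The correlations, dropout slopes and attrition splits are assumptions, so no single figure for the residual bias can be attached to this trial. The argument for the 3-month LIDAS depends least on them, because an episode reported there bears directly on 12-month incidence whatever drives dropout. The weakness lies in a secondary analysis. It reduces what agreement with the primary result can show and does not itself make the primary result wrong.

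**What to change.** Include 3-month LIDAS status and a small set of early symptom scores in the imputation model, for example 3-month PHQ-9 and one summary of the weekly PHQ-2/GAD-2; or state that 3- and 12-month outcomes are imputed jointly. The weekly summary also helps for participants who missed month 3. Add the same measures to the regressions that examine missingness of the 12-month outcomes.

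All these variables are already collected, and recruitment was still open when the article was published, so the cost is SAP wording and slightly more programming. The auxiliary set must stay small, given about 39 expected observed events in the app arm and because the auxiliaries will themselves be partly missing.
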